**Table 11.2.1. Clinical and Radiologic Assessment:**

**Please see CTSU website for relevant forms for MRI and clinical/endoscopic response.**

Please see CTSU website for endoscopic and MRI assessment of response video by [name]. Please contact [name] with questions about this section (see face page for contact information). [Alliance A022104 \(JANUS\) Trial Webinar - October 2023 \(youtube.com\)](#)

| MSK Regression Schema# |                                                                                                                                                                                                                                                                                                                                                  |                                                                                                                                                                                                                                                                                    |                                                                                                                                                                                                                                                                                                                                                                                  |
|------------------------------------------|--------------------------------------------------------------------------------------------------------------------------------------------------------------------------------------------------------------------------------------------------------------------------------------------------------------------------------------------------|------------------------------------------------------------------------------------------------------------------------------------------------------------------------------------------------------------------------------------------------------------------------------------|----------------------------------------------------------------------------------------------------------------------------------------------------------------------------------------------------------------------------------------------------------------------------------------------------------------------------------------------------------------------------------|
|                                          | Clinical Complete Response                                                                                                                                                                                                                                                                                                                | Near Complete Response                                                                                                                                                                                                                                                      | Incomplete / No Response                                                                                                                                                                                                                                                                                                                                                  |
| Endoscopy                         | 
 
Flat, white scar
 
Telangiectasia
 
No ulcer
 
No nodularity
 
                                                                                                                                                                                                              | 
 
Irregular mucosa
 
Superficial ulceration
 
Mild persisting erythema of the scar
 
                                                                                                                                   | 
 
Visible tumor
 
                                                                                                                                                                                                                                                                                                                  |
| Digital Rectal Exam               | 
 
Normal^
 
                                                                                                                                                                                                                                                                             | 
 
Smooth induration or minor mucosal irregularity^
 
                                                                                                                                                                      | 
 
Palpable tumor nodules^
 
                                                                                                                                                                                                                                                                                             |
| MRI-T2WI                          | 
 
Normal appearing rectal wall
 
 
OR
 
 
Only fibrosis (dark T2 signal) and no intermediate signal intensity at the site of tumor*
 
 
AND
 
 
No suspicious lymph nodes (Table Y)
 
 | 
 
Predominantly fibrosis at the site of tumor* with punctate areas of T2 intermediate signal
 
 
AND/OR
 
 
No suspicious or borderline enlarged lymph nodes (Table Y)
 
 | 
 
Predominantly residual tumor with T2 intermediate signal and no or minimal fibrosis at the site of tumor*
 
 
AND/OR
 
 
Suspicious lymph nodes (Table Y)
 
 
AND/OR
 
 
Mucin at the site of tumor***
 
 |
| MRI-DW                            | 
 
No restricted diffusion** at the site of tumor*
 
                                                                                                                                                                                                                          | 
 
Punctate areas of restricted diffusion** at the site of tumor*
 
                                                                                                                                             | 
 
Restricted diffusion** at the site of tumor*
 
                                                                                                                                                                                                                                                             |

\* Site of tumor: rectal wall, extramural vascular invasion and/or tumor deposit.

\*\* Restricted diffusion: high signal on DWI high b-value (minimum b800) and low signal on ADC map. *T2 dark through* (low signal on both DWI and ADC map) and *T2 shine through* (high signal on both DWI and ADC map) effects are not considered restricted diffusion.

\*\*\* MRI is unable to differentiate cellular from acellular mucin.

# Clinicians can also refer to the following website for examples of cCR, nCR, and iCR:  
<https://nomtrial.mskcc.org/Home/Index>

^ Note not all tumors can be palpated (e.g., 10-11 cm from the anal verge) and thus the endoscopic features will be paramount and take precedent for decision-making in these mid-rectal tumors along with the MRI features (questions in this regard can be addressed by [name] (email above) or [name] (email above) or both).

**Table 11.2.2.** Radiological criteria of suspicious lymph nodes on restaging MRI rectum.

| Anatomic Location                                            | Restaging MRI rectum                         |
|--------------------------------------------------------------|----------------------------------------------|
| TME (mesorectal, superior rectal)                            | > 5 mm                                       |
| Internal iliac                                               | > 4 mm                                       |
| Obturator                                                    | > 6 mm                                       |
| M1 (inguinal, external iliac, common iliac, retroperitoneal) | > 10 mm                                      |
| Mucin within the lymph node                                  | Suspicious regardless the size or location * |

\* MRI is unable to differentiate cellular from acellular mucin.

**Table 11.2.3 Radiologic Features of Re-Growth**

|         | Signs of Re-Growth                                                                                             |
|---------|----------------------------------------------------------------------------------------------------------------|
| MRI-T2W | New Intermediate T2 Signal, No T2 Scar
AND/OR
New Lymph Nodes
AND/OR
Increased Size of Lymph Nodes |
| MRI-DW  | New Signal on B800-B1000                                                                                       |

### 11.3 Pathological Tumor Response at TME

For all patients who undergo surgery, all operative and pathology reports for the TME resection must be submitted. Reports must contain information about microscopic involvement of surgical resection margins.

#### 11.3.1 Definition of Surgical Margin Status and Overall Completeness of TME Resection

##### Margin Type:

|                  |                                                                                                                         |
|------------------|-------------------------------------------------------------------------------------------------------------------------|
| Proximal Margins | The proximal surgical margin refers to the most cephalad portion of the specimen (closest to patient's head).           |
| Distal Margins   | The distal margin refers to the most caudad portion (closest to anal canal).                                            |
| Radial Margins   | The radial margin, synonymously termed circumferential margin refers to the outer circumference of the rectal specimen. |

##### Margin Positivity:

|          |                                                                                                                                     |
|----------|-------------------------------------------------------------------------------------------------------------------------------------|
| Positive | A surgical margin is POSITIVE if the pathologist notes tumor within $\leq$ 1mm of any edge of the primary tumor specimen.           |
| Close    | A surgical margin is CLOSE if the pathologist notes tumor $> 1$ but $\leq$ 3mm of any edge of the primary tumor specimen.           |
| Negative | A surgical margin is NEGATIVE if the pathologist notes that there is NO tumor within 3mm of any edge of the primary tumor specimen. |

##### Overall Completeness of TME Resection:

This categorization schema should focus on the pelvic resection of the TME specimen. If distant tumor is appreciated intraoperatively (for example, a liver metastasis), the pelvic resection may still be considered R0.

|              |                                                                                                                                                                                                                                                                                                                                                                                                                                                                                                                                                         |
|--------------|---------------------------------------------------------------------------------------------------------------------------------------------------------------------------------------------------------------------------------------------------------------------------------------------------------------------------------------------------------------------------------------------------------------------------------------------------------------------------------------------------------------------------------------------------------|
| R0 resection | All gross disease has been removed, and microscopic examination reveals all surgical margins free of tumor. This must include the proximal, distal and radial margin.
Tumor > 1mm from the tumor resection margins is considered R 0 . In some cases, intraoperatively, a surgeon may biopsy a liver nodule or retroperitoneal node. Resection will still be considered curative if pathologic examination reveals positive lymph nodes as long as the nodes were completely resected, unless there is also evidence of positive margins. |
| R1 resection | There is evidence of tumor manifest at 1 or more surgical resection margins based on microscopic pathologic assessment of the tumor specimen but there is no macroscopic evidence of tumor at any resection margin nor is there macroscopic evidence of residual tumor based on the surgeon's operative report.                                                                                                                                                                                                                                         |
| R2 resection | The surgical pathologist identifies any macroscopic evidence of tumor at any of the surgical resection margins or there is macroscopic evidence of residual tumor based on the surgeon's operative report.                                                                                                                                                                                                                                                                                                                                              |
| No resection | Removal of the primary tumor was not performed.                                                                                                                                                                                                                                                                                                                                                                                                                                                                                                         |

### 11.3.2 Degree of Pathological Treatment Response

#### Pathological Complete Response (pCR):

A pCR must include no gross or microscopic tumor identified anywhere within the surgical specimen. This must include: No evidence of malignant cells in the primary tumor specimen **AND** No lymph nodes that contain tumor.

#### Pathological Response other than a Complete Response:

The definition of a non-pCR will include any surgical specimen that has any evidence of residual tumor manifest in the primary or regional lymph nodes.

For patients who do not meet criteria for a pCR, the extent of response to pre-operative therapy will be graded using the Tumor Regression Grade (TRG) schema. This schema evaluates the degree to which the primary rectal tumor specimen has responded to neoadjuvant treatment.

#### Tumor Regression Coding Based on AJCC 8th Edition

| Tumor Regression Grade (TRG) | Response Categorization | Description                                                                                                |
|-------------------------------------|--------------------------------|-------------------------------------------------------------------------------------------------------------------|
| TRG-0                               | Complete                       | No viable cancer cells                                                                                            |
| TRG-1                               | Moderate                       | Single cells or rare, small groups of cancer cells                                                                |
| TRG-2                               | Minimal                        | Residual cancer showing evident tumor regression, but more than single cells or rare small groups of cancer cells |
| TRG-3                               | Poor                           | Minimal or no tumor kill; extensive residual cancer and no evident tumor regression                               |

### 11.4 Disease Evaluation after TME

Disease evaluation for all patients after completion of surgery. Patients will be evaluated as per the schedule of tests noted in Section 5.0. At the time of evaluation, patients will be classified in the following manner:

- No evidence of disease (NED)
- Recurrence of disease (REC): The appearance of rectal carcinoma in the primary site, nodal basin or distant organ sites during follow-up will be classified as recurrence cancer. Recurrence will be classified as local or distant.

|                           |                                                                                          |
|---------------------------|------------------------------------------------------------------------------------------|
| Local recurrence   | Any tumor located in the pelvis or the perineal scar after TME has been completed |
| Distant recurrence | Any tumor outside the pelvis and the perineal scar; can occur prior to or after TME      |

Patients may have local recurrence, distant recurrence, both or neither. Imaging should be used to document the extent of local and distant disease recurrence. Pathological confirmation of suspected distant metastasis should be performed based on clinical judgment and is not mandated.

Although pathologic confirmation of recurrence is not mandated, local and distant recurrences will be categorized based on supporting evidence. Recurrences will be categorized based on whether they are evident from:

|                             |                                                                                                                                                                                                        |
|-----------------------------|--------------------------------------------------------------------------------------------------------------------------------------------------------------------------------------------------------|
| Pathology:           | Use this category if there is any pathology or cytology demonstrating recurrent rectal cancer.                                                                                                         |
| Serial Imaging:      | Use this category is for recurrences that have not been confirmed by pathology but where serial imaging studies (serial is defined as similar scans performed more than 30 days apart) indicate tumor. |
| Clinical Evaluation: | Use this category for recurrences that have not been confirmed by pathology or serial imaging studies but are manifest on physical exam or compelling imaging studies (absent serial images).          |

- Second primary colorectal cancer

Second primary cancers are those that arise anywhere in the colon. Tumors involving the surgical anastomosis or arising from the pelvis are to be categorized as recurrent disease.

## 12.0 END OF TREATMENT/INTERVENTION

### 12.1 Duration of Protocol Treatment

During neoadjuvant treatment, protocol treatment (intervention) is to continue until completion of LCRT and 8 cycles of consolidation chemotherapy, distant disease progression, local/regional disease progression which precludes surgery, or unacceptable adverse events. After neoadjuvant treatment, TME will be performed when it is appropriate (incomplete response to assigned TNT regimen (e.g. residual tumor remains, no evolution to complete response). Please see the study calendar (Section 5) and the treatment section (Section 7) for treatment and follow-up time periods.

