# CAPOX = 5 cycles (1 cycle = 3 weeks)

Treatment is to continue for the full course of LCRT and Arm 1 or Arm 2 chemotherapy unless there is a clinical reason to stop. Following neoadjuvant chemotherapy, patients will either proceed to surgery (TME) or watch & wait (WW). Patients will be followed for 5 years or until death, whichever comes first.

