## 7.0 TREATMENT PLAN/INTERVENTION

Protocol treatment is to begin  $\leq 28$  days of registration.

For questions regarding treatment, please see the study contacts page.

It is acceptable for individual chemotherapy doses to be delivered  $\leq$  a 24-hour (1 business day) window before and after the protocol-defined date for Day 1 of a new cycle. For example, if the treatment due date is a Friday, the window for treatment includes the preceding Thursday through the following Monday. In addition, patients are permitted to have a new cycle of chemotherapy delayed up to 7 days for major life events (e.g., serious illness in a family member, major holiday, vacation that cannot be rescheduled) without this being considered a protocol violation. Documentation to justify this delay should be provided.

Protocol therapy will consist of neoadjuvant chemoradiation followed by neoadjuvant consolidation chemotherapy. Neoadjuvant chemoradiation includes radiation (45Gy + 9 Gy boost) in combination with a fluoropyrimidine (preferred capecitabine; permissible substitution: 5-Fluorouracil continuous infusion).

Subsequently, patients will receive eight cycles of chemotherapy with mFOLFOX6 (may be substituted by 5 cycles of CAPOX) in the control arm or eight cycles of chemotherapy with mFOLFIRINOX in the experimental arm. All patients will undergo assessment 8-12 weeks post-completion of this therapy for the primary endpoint of cCR and based on this assessment recommended further management with watch and wait, repeat assessment 8 weeks later, or surgery

In patients requiring surgery, it may begin any time after assessment for primary endpoint, i.e. 8-12 weeks following completion of chemotherapy.

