### 12.2 Criteria for Discontinuation of Protocol Treatment/Intervention

In the absence of treatment delays due to adverse event(s), treatment may continue until one of the following criteria applies:

- Disease progression during neoadjuvant treatment which precludes surgery (e.g., tumor perforation that prohibits completion of treatment or treatment as designated per Arm or detection of distant metastases)
- Intercurrent illness that prevents further administration of treatment
- Unacceptable adverse event(s)
- Patient decides to withdraw from the study
- General or specific changes in the patient's condition render the patient unacceptable for further treatment in the judgment of the investigator
- Clinical progression
- Patient non-compliance
- Pregnancy (if applicable)
  - All women of child bearing potential should be instructed to contact the investigator immediately if they suspect they might be pregnant (e.g., missed or late menstrual period) at any time during study participation.
  - The investigator must immediately notify CTEP in the event of a confirmed pregnancy in a patient participating in the study.
- Termination of the study by sponsor

The reason(s) for protocol therapy discontinuation, the reason(s) for study removal, and the corresponding dates must be documented in the Case Report Form (CRF).

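### Sections 12.1 and 12.2 do not consistently say whether local progression that remains resectable ends neoadjuvant protocol treatment

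*Combined protocol and SAP*

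**What the plan says.** Section 12.1 states that "protocol treatment (intervention) is to continue until completion of LCRT and 8 cycles of consolidation chemotherapy", or until one of these occurs: "distant disease progression, local/regional disease progression which precludes surgery, or unacceptable adverse events". Distant progression ends treatment without condition. Local or regional progression ends it only when it rules out surgery.

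Section 12.2 says that "treatment may continue until one of the following criteria applies". Its first bullet is "Disease progression during neoadjuvant treatment which precludes surgery", with examples. A separate bullet further down says only "Clinical progression". The protocol does not define that term.

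The notes to the schema say that treatment runs for the full course "unless there is a clinical reason to stop".

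On cycle numbers, 12.1 speaks of "completion of LCRT and 8 cycles of consolidation chemotherapy" for all patients. Section 7.0 says that the control regimen "may be substituted by 5 cycles of CAPOX", and Section 7.2 and Table 7.2.2 agree. Section 12.1 closes by referring the reader to Sections 5 and 7 for treatment and follow-up periods.

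**The concern.** The resectability limit appears twice, in 12.1 and in the first bullet of 12.2, so it looks deliberate. If the unqualified bullet also governs local growth, the limit does nothing: any clinically evident local growth would already meet a stopping criterion. If the unqualified bullet is meant more narrowly, the protocol does not say how. An investigator whose patient has local growth that is still resectable cannot tell from the text which statement applies.

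The situation can arise. The study calendars schedule digital rectal examination and sigmoidoscopy at about week 10, before chemotherapy starts. Rectal MRI is scheduled only at baseline and at weeks 32-38. Local growth during treatment would therefore be found mainly by examination or symptoms, which is the kind of finding the undefined term suggests.

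At stake is whether sites, and possibly arms, apply the same stopping rule in a trial that monitors treatment completion and defines analysis populations by chemotherapy received.

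**Working it through.** No alpha, power or sample-size figure is involved, so the check sets the texts side by side.

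**Step 1. Apply each statement to one case:** local growth during neoadjuvant treatment, still resectable, no distant disease, no unacceptable toxicity.

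| Statement | Result |
|---|---|
| 12.1 | No stopping event; continue |
| 12.2, first bullet | Not met; surgery is not ruled out |
| 12.2, later bullet | Met, if read as written |

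The inconsistency lies inside 12.2 as well as between 12.1 and 12.2.

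**Step 2. Look for a passage that settles it.**
- The schema note is general and does not say whether resectable growth is a reason to stop.
- The surgery recommendation in 7.3 concerns the assessment after neoadjuvant therapy is complete.
- The discontinuation text in 8.2 concerns recurrence and second malignancy.
- Section 12.4 concerns protocol constraints that harm the patient, or a patient who no longer wishes to continue.

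None settles the case.

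**Step 3. Trace the consequences.**
- *mITT (13.4.1)*, used for the phase II cCR test, needs completed LCRT and at least one dose of protocol chemotherapy. A patient stopped at the week-10 visit leaves the cCR denominator; the same patient continued stays in it.
- *Per-protocol (13.4.1)* needs at least three cycles, so stopping before the third cycle removes an otherwise eligible patient.
- *Early off treatment (13.5.1)* counts patients who receive fewer than 8 cycles because of progression, among other reasons. Stopped after the first dose, the patient is an event; continued to the end, a completer.
- *Follow-up (12.3.1)* leaves MRI, endoscopy, CT and CEA to the treating team once a patient is off treatment early, for progression or for other reasons. Resectable local growth during treatment is not among the DFS events in 13.1.1, so this patient remains at risk for DFS while the assessment schedule may lapse.
- *Phase III ITT membership* is unaffected.

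**Step 4. Scale of the 13.5.1 rule.** Multiply each trigger difference by patients per arm:
- 0.220 × 44 = 9.7, so 10 patients are needed to exceed it;
- 0.104 × 87 = 9.05, so 10;
- 0.067 × 131 = 8.8, so 9.

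The triggers correspond to a between-arm excess of 9 or 10 patients. This shows the scale on which unevenly handled patients would register. It does not estimate how many there will be.

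**Step 5. Cycle count.** Five CAPOX cycles are stated consistently in 7.0, 7.2, Table 7.2.2 and the schema notes. Sections 12.1 and 13.5.1 mention only 8. A patient who finishes five CAPOX cycles as planned has not stopped for a reason listed in 13.5.1 and so should not be counted, but the definition gives no completion threshold for that regimen.

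**The case against.** The strongest reply is that 12.1 summarizes duration and is not a closed list. It omits withdrawal, pregnancy, non-compliance and intercurrent illness, all of which are in 12.2, and nobody would call those contradictions. Section 12.2 is permissive in tone, has a bullet for investigator judgment, and may use the undefined term for symptomatic deterioration or for a later phase. The early-off-treatment definition already counts stops at the physician's discretion, so an early stop counts whichever bullet is used. Both arms work under the same text, and crossing a 13.5.1 boundary leads to review, not to an efficacy decision.

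Much of this stands, and it rules out stronger readings that a reader might infer:
- *Two directly opposed commands.* Not supported. The word any does not appear in the 12.2 bullet, and the investigator-judgment bullet means that no site is compelled to continue in a patient judged unfit for it.
- *Immediate surgery under one section and a full further course of chemotherapy under the other.* Not supported. Section 12.2 says nothing about surgery after discontinuation, and the contrast depends on reading 12.1 in isolation.
- *Eight CAPOX cycles, with the cumulative oxaliplatin dose that implies.* Not supported. Section 12.1 itself sends the reader to Section 7, and no treatment table contains such a regimen.

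The reply does not remove the central point. On local progression 12.1 is not merely silent: it states a limit, and 12.2 repeats it. The alternative meanings offered for the later bullet are possible, but none is written down.

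**Conclusion.** The inconsistency is real and should be corrected. The protocol limits local progression as a stopping event to cases that rule out surgery, then lists an unlimited and undefined progression event beside it. It does not consistently say whether resectable local growth ends protocol treatment.

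The consequence is possible variation between sites in cycles received, mITT and per-protocol membership, early-off-treatment counts and continued scheduled assessment. Its size cannot be computed, since no rate of resectable local progression during neoadjuvant therapy is given, and any between-arm effect would further require that rate or its handling to differ by arm. The conclusion assumes that the later bullet in 12.2 means what it says and applies during neoadjuvant treatment. The cycle-count mismatch is a minor wording matter.

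**What to change.** 1. Reconcile 12.1 with both progression bullets of 12.2, so that one statement says how local progression that remains resectable is handled. Which rule applies is for the study team.
2. Define the undefined progression term in 12.2, or cross-reference it to a definition.
3. Use the same event in the 13.5.1 early-off-treatment definition.
4. Minor: word the cycle counts in 12.1 and 13.5.1 by regimen, so that they match the 5-cycle CAPOX option already in Section 7.

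The cost is protocol wording only, with no change to sample size, boundaries or planned tests.
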